#### Neuroimaging methods

##### Imaging acquisition

All images are acquired using a 3-Tesla whole-body MR system (Siemens MAGNETOM TIM Trio, Siemens Medical Solutions, Erlangen, Germany). The MR imaging protocol includes: (1) a 3-D anatomic volume (8 min); (2) resting-state functional connectivity (7.5 min); and (3) diffusion tensor imaging (DTI) (30 min); acquisition for a total of under 60 min of scanning. The anatomic imaging will be conducted for anatomic reference in fMRI data analysis and volumetric analysis
[85]. The DTI images will be used to refine selection of regions-of-interest (ROI) for model-based analyses
[82,86,87]. The baseline/resting fMRI acquisition will be used to measure region connectivity. The Positive and Negative Affective Scale will be administered before and after the scanning session to assess emotional states at the time of the fMRI
[88].

##### Molecular genetic predictors

We collect whole blood for DNA extraction, and for DNA and lymphoblast banking at the Rutgers Cell & DNA Repository (
http://www.rucdr.org/) from every consenting patient at the screening visit. DNA will be used for genotyping genetic polymorphisms, mostly single nucleotide polymorphisms (SNPs), in a series of candidate genes that have emerged from previous human or animal studies or the ongoing genome-wide association studies thought to be relevant for antidepressant treatment response, including genes from the HPA-axis, monoaminergic systems, or neurotrophic systems
[89]. The study was not powered to test for genome-wide association; however, data from it might be useful in meta-analyses across studies. The main intent of the DNA analyses is to examine hypothesized molecular genetic predictors in conjunction with other clinical and biological predictors to identify subtypes of patients more likely to respond to or remit with one of the three study treatments. DNA is also collected for future investigation of epigenetic modifications, including DNA methylation
[90]. We extract RNA from whole blood collected in Tempus blood RNA tubes (Applied Biosystems) at the baseline visit after randomization and after 2 and 12 weeks of treatment. Analyses measure the expression of specific candidate transcripts encoding chaperone and co-chaperone proteins of the glucocorticoid receptor, using real-time PCR as well as gene-expression microarrays for a more comprehensive characterization of blood gene expression profiles
[91]. We also assess the correlation of these gene-expression patterns with other putative biomarkers (for example, the Dex/CRH test and inflammatory markers) and test whether they can be used to predict or monitor treatment response
[92].

##### Neuroendocrine function

The Dex/CRH test has been used to assess HPA axis function in depressed patients
[93]. This test involves oral administration of dexamethasone at 2300 h the night prior to the assessment, followed by intravenous CRH administration at 1500 h the following afternoon. The CRH can be administered as a fixed dose of 100 mg of human CRH or 1 mg/kg of ovine CRH. At 1500 h, prior to the CRH infusion, and at set intervals for the following 2 h, plasma samples are collected for cortisol and adrenocorticotropic hormone (ACTH). In healthy subjects, there is little increase in concentrations of cortisol or ACTH after administration of CRH because the CRH can only minimally override the HPA-suppressing effects of dexamethasone. In many patients with MDD, however, this test induces substantial increases in plasma ACTH and cortisol concentrations
[94]. The mechanism behind this effect is presumed to be impaired signaling of the glucocorticoid receptor (GR)
[95]. Reduced GR sensitivity diminishes the ability of dexamethasone to suppress the HPA axis at the level of the pituitary, and it also reduces the inhibition of CRH and arginine vasopressin release from the paraventricular nuclei of the hypothalamus, consequently enhancing the stimulatory effects of the exogenously administered CRH
[96].

Use of the Dex/CRH test in several studies has demonstrated HPA axis dysregulation during a major depressive episode, and normalization of the axis after recovery
[95,97,98]. Sustained non-suppression of the HPA axis in MDD patients undergoing the Dex/CRH test predicts a worse prognosis for treatment response
[94,99]. Some data also suggest that this test may predict the risk of depressive relapse
[100]. The Dex/CRH test is well tolerated in medically healthy subjects
[101].

For the PReDICT protocol, we conduct the Dex/CRH test immediately prior to randomization and at the end of the 12-week acute phase treatment period, using the protocol described by Heim *et al*.
[102]. We used human CRH for study participants during the first 2 years of the study. However, the manufacturer subsequently experienced production difficulties, causing us to switch to ovine CRH for the remainder of the study.

##### Inflammatory markers

A plethora of studies have confirmed that medically healthy subjects with major depression demonstrate increased circulating concentrations of the proinflammatory cytokines tumor necrosis factor (TNF)-alpha, interleukin (IL)-1-beta, and IL-6 as well as acute phase reactants, especially C-reactive protein (CRP)
[103-105]. Associations between depression and increased proinflammatory cytokines or CRP have been apparent across the adult life span, whether comparisons are made between clinically depressed patients and matched controls
[106] or whether they arise from large population-based studies
[107,108]. Recent investigations have reported positive correlations between levels of various inflammatory mediators and depressive symptom severity; furthermore, the association between immune activation and depression appears to be robust enough to be detectable in the context of mild depressive symptoms that do not meet criteria for major depression
[109]. Supportive of the idea that inflammation is involved in the broader pathophysiology of MDD, therapeutic administration of cytokines promotes the development of frank depressive symptoms and syndromes. For example, 40% to 50% of patients receiving chronic treatment with interferon-alpha (which induces the production/release of IL-6, IL-1b, and TNF-alpha) develop clinically important depressive symptoms or meet criteria for major depression within 3 to 6 months of treatment initiation
[110]. Relevant to the pathophysiology of major depression, proinflammatory cytokines are potent activators of corticotropin-releasing hormone (CRH) pathways (that is, the HPA axis and sympathetic nervous system)
[111]. Cytokines appear capable of inhibiting glucocorticoid receptor functioning
[112] and of diminishing CNS serotonin signaling capacity by reducing tryptophan bioavailability and by increasing presynaptic serotonin reuptake activity
[113,114].

IL-6 and CRP assessment: To further clarify whether IL-6 and CRP are predictors of treatment response (early or final), plasma collected at baseline, at a point early in treatment, and at week 12 will be analyzed for concentrations of IL-6 and CRP. Plasma concentrations of IL-6 will be determined in duplicate using sandwich ELISA according to manufacturer‘s protocol (R & D Systems, Minneapolis, MN, USA)
[115]. The mean inter- and intra-assay coefficients of variation for control samples in this assay are reliably 10% or less
[116].

Plasma CRP will be assessed with a high-sensitivity turbidimetric assay based within the Emory University Hospital Clinical Laboratories. Sensitivity of the assay is rated at 0.18 mg/L, detection limits of the assay are 0.2 to 80 mg/L, and functional sensitivity (at 20% CV) is 0.2 mg/L.

##### Personality

Prior research suggests that personality variables, including personality disorders (PDs), predict the longitudinal course of MDD in treatment-seeking patients
[117,118], although data on personality predictors of response to specific treatments are sparse
[119]. Perhaps the central question at the heart of current research on the classification of personality pathology, which bears on predictors of treatment outcome, is how best to conceptualize personality: as categorical PDs; as sums of numbers of PDs or PD criteria met
[117]; as dimensional representations of syndromes (for example, personality prototypes, for which patients can vary in the degree to which they match a given diagnosis
[120]); or as dimensional traits (for example, neuroticism, emotional dysregulation, or emotional avoidance)
[121,122].

We addressed these issues in this study by using measures that cover the landscape of personality and PD diagnosis: (1) The Shedler-Westen Assessment Procedure, 2^nd^ edition (SWAP-II), an instrument developed for use by clinically expert observers (much like the HRSD for depression), which yields dimensional DSM-IV PD diagnoses, empirically-derived PD syndromes, empirically-derived traits, and empirically-derived scales that describe patients whose MDD did and did not respond to various forms of treatment in naturalistic settings
[123]; and (2) the International Personality Disorders Examination (IPDE)
[124], a semi-structured interview that can yield categorical and dimensional data on both the DSM-IV and ICD-10 PDs.

##### Clinical and demographic variables

Clinical and demographic variables are collected by self-report measures and structured interviews. Demographic data on gender, age, race, ethnicity, education level, marital status, employment status, and living situation are collected from an intake form completed at the screening visit. Family psychiatric history is collected using a self-report form listing major Axis I diagnoses and suicide, and inquiring which, if any, family members were affected.

Among the data for clinical variables collected are the self-reported history of childhood trauma using the CTQ and EHEI, and recent important life events from the Life Experiences Survey
[76]. The self-report Goals scale
[125] and Combined Hassles and Uplifts scale
[126] assess current levels of hopelessness and frustration and are collected at baseline and at intervals throughout the acute and follow-up phases. Depression and anxiety severity are assessed by both clinician interview (HDRS, MADRS, HARS) and self-report forms (QIDS, BDI). History of substance abuse and dependence and presence of co-morbid psychiatric conditions are obtained from the SCID interview.

#### Data management

A local area network resident relational database (Microsoft Office Access 2010, Microsoft, Redmond, WA, USA) serves as the secure repository for study data. The relational structure of the database has been optimized via conformity to established guidelines for data normalization
[127]. All tables in the relational database fulfill criteria for third normal form at a minimum, thereby ensuring structural optimization of the database
[127].

The central tables in the relational database include: (1) [Subject] table with one row per participant and each row uniquely identified by a HIPAA-compliant subject number
[128]; and (2) [Subject Contact] table with one row per participant visit and each row uniquely identified by the combination of the subject number and contact date. Other dependent tables store data regarding phase of study participation and collection and tracking of biological samples including aliquot management and recording of results. Database security is ensured by hierarchical password-secured access beginning with password-restricted access to the network followed by password-restricted access to the database itself. The database security helps to maintain in the masking of research staff to randomized treatment by restricting access to certain segments of the data.

The relational database also aids in assuring data integrity. Real-time (point-of-entry) data validation is implemented by utilizing: (1) data rules imposed by the table-to-table relationships of the normalized data (for example, it is impossible to enter rating scale data on an erroneous visit date); (2) item-level range checks and compatibility checks; (3) double entry of all scales with automated checking for discrepancies; and (4) summary checks of psychometric scales utilizing mirrored (redundant) data entry. Other data validation measures include automated import of laboratory results (eliminating transcription errors) and regular review of automatically-generated data compatibility reports (for example, report flags as a possible error when CGI and HDRS values for a patient visit appear to be incompatible, triggering review of previously entered data).

Finally, the optimized structure of the relational database has enabled the *a priori* development and implementation of queries and reports that service routine outside reporting needs (for example, reporting to study sponsor, data safety monitoring board, institutional review board), internal tracking of progress toward completing study objectives, and export of HIPAA-compliant study data for import into external statistical software packages for data analysis. In addition, the normalized structure of the database simplifies fulfillment of *ad hoc* data requests for additional novel purposes including preliminary data for other applications, abstract submission, and data sharing.

#### Data analyses

The primary data analyses consist of two phases: (1) identification of significant predictors of treatment response, both overall and treatment-specific; and (2) building of a comprehensive model of treatment response similar to those which predict remission and response to treatment as well as those who suffer a recurrence
[129]. The first phase will use various variable selection methods (for example, recursive partitioning
[130,131]), as well as different measures of discriminating ability (for example, C statistic or ROC
[132], net reclassification improvement
[133]), to determine the best set of predictors that are both statistically significant and clinically important using predefined importance criteria. The building of the prognostic model will use established techniques
[134] to create a model of treatment response that can then be tested in future research, including quantifying predictors, calibrating the model, and possibly adapting it to the clinic using a points method. All analyses will be performed in Stata 12.

#### Statistical power/sample size

There are no established ways to determine sample size for the identification of possible predictors of an outcome, as it is a fact-finding endeavor and does not test specific *a priori* hypotheses. However, the issue of clinical importance is much more paramount in a study of this nature (that is, while statistically significant predictors are of interest, it is also necessary to determine if the predictors of interest result in a large enough absolute or relative difference in response between those with and without the predictor to be clinically meaningful)
[135]. In addition, it is clear that smaller but statistically significant effects will likely be difficult to replicate and thus reduce the validity of the model for future use. Given the sample size we intend to recruit over the time period specified, we will illustrate the effect sizes for treatment remission versus non-remission, as very few data on differential treatment response are available. For these calculations, we assume a 40% remission rate. The detectable difference is defined as the difference (either mean or proportion) between the population and the treatment remitters detectable with the given sample size, a Type I error rate (α) = 0.01, and a statistical power of 0.80. We chose an α = 0.01 because the nature of the model building will require the testing of multiple predictors. Population values are determined from various published and unpublished data (Table
1). 

**Table 1 T1:** Sample effect size calculations for selected variables

		**Monotherapy treatment remission (*****n*** **= 400)**		**Combination treatment remission (*****n*** **= 240)**	
**Variable of interest**	**Observed value in the population [mean (SD) or % positive]**	**Detectable difference***	**Effect size (difference relative to variation)**	**Detectable difference***	**Effect size (difference relative to variation)**
Endpoint HDRS score	16.0 (4.9)	−1.9	0.39	−2.5	0.51
Serotonin transporter gene carriers (minor allele carriers/Caucasian)	59.9%	17%	0.31	22%	0.40
Elevated C-reactive protein (>0.22 mg/dl)	21%	13%	0.36	16%	0.48
fMRI brain score	44.1 (4.3)	1.7	0.40	2.2	0.51
Baseline Dex/CRH response (cortisol AUC, (ng*min)/mL)	2730.6 (266)	104.6	0.39	136.1	0.51
Interleukin-6 (pg/mL)	6.3 (1.4)	0.6	0.43	0.7	0.50

Thus a sample size of 400 will be adequate to detect moderate to large effect sizes in treatment remission predictors
[136]. Although the sample sizes for differential remission by treatments will be less, with a projected overall remission rate of 30% in any group, there will be approximately 40 remitters in each group to detect the statistically significant interactions. These are reasonable numbers for the detection of large interaction effect sizes
[136].

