[12,13]. Despite these advances, depression treatment continues to be hampered by two major limitations: an unacceptably low rate of symptomatic remission, and the virtual absence of any practical predictors of treatment response, whether partial or complete. Although it is widely considered that current interventions benefit approximately 60% of MDD patients, only about 30% to 40% of patients show full remission of their symptoms as defined by the MacArthur criteria (for example, a 17-item Hamilton Depression Rating Scale (HDRS) score <8)
[14,15]. Approximately 30% more demonstrate some response to treatment, indicating they experience clinically important reductions in their depressive symptom burden, yet also continue to experience clinically important residual symptoms. Patients who experience a response short of remission are more vulnerable to relapses and recurrences of the disorder
[16] and experience greater functional disability
[17].

Current treatment for MDD involves a trial-and-error approach because there are no consistently identified predictors of differential response across treatment modalities. Primary first-line treatments consist of either an evidence-based form of psychotherapy or antidepressant medication. In patients treated pharmacologically, several treatment options are available, but there are very few clinical trial data to guide clinicians as to which first step enhances the odds of remission for an individual patient
[18]. Illustrating the importance of such trials, one retrospective study found a differential advantage for psychotherapy over medication (nefazodone) in chronically depressed patients with early life trauma
[19]. A treatment regimen that ultimately proves to be ineffective results in continuing patient distress and role dysfunction, discouragement regarding possible relief from MDD, exposure to potential side effects, and unnecessary medical costs. Among the roughly 70% of depressed patients who do not remit with their first treatment, many do not return to explore other treatment options that might have proven effective
[20].

Previous efforts attempting to identify predictors of treatment response have typically been *post-hoc* analyses of datasets designed to test other hypotheses

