## Methods/design

### Overview

Four hundred^a^ treatment-naïve patients with a primary diagnosis of MDD and HDRS-17 scores ≥18 at screening and ≥15 at the baseline visit are to be randomly assigned equally to one of three possible treatments: (1) a selective serotonin reuptake inhibitor (SSRI, escitalopram); (2) a serotonin norepinephrine reuptake inhibitor (SNRI, duloxetine); or (3) individual cognitive behavior therapy (CBT). Initial treatment consists of a 12-week course with one of these monotherapies. Patients who meet criteria for full remission of their MDD are followed for a 21-month follow-up phase to monitor for depression recurrence. Patients who do not remit after the 12-week monotherapy acute treatment phase are offered another 12 weeks of acute treatment, during which they receive combination therapy with study medication plus CBT. The overall study design is presented in Figure
1.

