#### Major endpoints

##### Remission

Remission, the study’s primary outcome measure, is defined as a HDRS-17 item total score <8 at both the week 10 and week 12 ratings visits for patients in the acute monotherapy phase. For patients who enter the combination treatment phase, remission is defined as a HDRS-17 item total score <8 at both the week 22 and week 24 ratings visits. Remitters from either the monotherapy or combination treatment phases are eligible to enter the long-term follow-up phase (21 months for monotherapy remitters; 18 months for combination remitters), returning every 3 months for assessments or until depression recurrence.

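### The power section plans the same primary endpoint on two unreconciled remission rates, 40% for Table 1 and 30% for the per-arm counts

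*Protocol article*

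**What the plan says.** All the planning figures are in the protocol article, under Statistical power/sample size.

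- Before Table 1: "For these calculations, we assume a 40% remission rate", with "a Type I error rate (α) = 0.01, and a statistical power of 0.80". Table 1 then has a monotherapy column at n = 400 and a combination column at n = 240.
- Directly after Table 1: "Thus a sample size of 400 will be adequate to detect moderate to large effect sizes in treatment remission predictors".
- Next, for differential prediction by treatment: "with a projected overall remission rate of 30% in any group, there will be approximately 40 remitters in each group". These counts are judged reasonable for detecting large interactions.

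The Overview says patients "are to be randomly assigned equally to one of three possible treatments", so each arm has about 133 patients. Under Major endpoints, remission in the monotherapy phase "is defined as a HDRS-17 item total score <8 at both the week 10 and week 12 ratings visits". That is the primary outcome, and no other endpoint is being planned in either paragraph.

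**The concern.** With equal allocation, the overall remission rate is the average of the arm rates. If every arm remits at 30%, the overall rate is 30% and cannot be 40%. The second paragraph does not call its 30% cautious, worst-case or specific to one arm; it calls it a projected overall rate. Per-arm numbers are smaller because the sample is divided by three, which gives no reason to lower the rate as well.

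Finding predictors of remission is the primary aim, and the number of remitters drives the precision of each remitter versus non-remitter comparison. The remitters-per-arm figure is also the only stated support for the interaction analyses. As printed, a reader cannot tell which scenario the trial is planned on.

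**Working it through.** **Inputs.** N = 400, three equal arms, rates 40% and 30%, α = 0.01, power 0.80, and the effect sizes in Table 1, all from the article. Sidedness is not stated; I take two-sided (z = 2.576). I compare remitters with non-remitters and, for binary predictors, put non-remitters at the tabulated population value.

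**Step 1: the plan's own counts.**

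| | at 40% | at 30% |
|---|---|---|
| Remitters, 400 × rate | 160 | 120 |
| Non-remitters, 400 × (1 − rate) | **240** | 280 |
| Remitters per arm, 133.3 × rate | 53.3 | **40** |

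The printed 240 comes out only at 40%, and the printed 40 per arm only at 30%. Three arms of 40 make 120 remitters, against the 160 behind Table 1.

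**Step 2: mean rows at n = 400.** Detectable standardized difference = (2.576 + z for power) × √(1/n₁ + 1/n₂).

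- 160/240, 80% power: (2.576 + 0.842) × 0.10206 = 0.349.
- 160/240, 90% power: (2.576 + 1.282) × 0.10206 = 0.394.
- 120/280, 80% power: (2.576 + 0.842) × 0.10911 = 0.373.

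Table 1 prints 0.39, 0.40, 0.39 and 0.43. These do not follow from the stated 0.80, but they do follow from about 90% power at 40%. The cortisol row shows it: 266 × 0.3937 = 104.7 against the printed 104.6. The 0.43 for interleukin-6 is a rounding effect: 1.4 × 0.3937 = 0.551, printed as 0.6, and 0.6/1.4 = 0.43. The combination column agrees: 96/144 at 90% power gives 0.508 against printed values of 0.50 to 0.51, while 80% power gives 0.450.

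Power of the printed effects at 120/280 is Φ(effect/0.10911 − 2.576):

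- 0.39: Φ(0.998) = 84%
- 0.40: Φ(1.090) = 86%
- 0.43: Φ(1.365) = 91%

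**Step 3: proportion rows at n = 400.** Two-proportion test with pooled variance under the null. At 160/240 and 80% power, the detectable decreases are 17.4 points from 59.9% and 12.5 points from 21% (13.0 with continuity correction). These match the printed 17% and 13%. For the 21% row, an increase would need 15.6 points, so the downward direction is the one that reproduces the table.

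Power of the printed differences at 120/280, with s₀ the pooled and s₁ the unpooled standard error:

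- 59.9% against 42.9%: s₀ = 0.0543, s₁ = 0.0538; Φ((0.17 − 2.576 × 0.0543)/0.0538) = Φ(0.56) = 71%.
- 21% against 8%: s₀ = 0.0411, s₁ = 0.0347; Φ((0.13 − 2.576 × 0.0411)/0.0347) = Φ(0.70) = 76%.

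At 160/240 the same formula gives 78% and 84%; the scatter around 80% comes from rounding the printed differences. At 120/280 the differences detectable with 80% power become 18.5 and 13.4 points, about 1 point larger.

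**Step 4: combination phase.** If all 280 non-remitters at 30% entered, and 30% of them remitted (84/196), the detectable effect at 80% power would be 0.446. The 40% scenario (96/144) gives 0.450, so this column is hardly affected.

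**The case against.** The strongest reply is that little depends on this. The article says there is no established sizing method for predictor discovery and presents the figures as illustrations. An endnote shows that 400 was set by recruitment. Moving from 0.349 to 0.373 leaves the moderate-to-large conclusion as it was. Using the lower rate for interactions errs on the safe side, since 40% would give 53 remitters per arm. Combination treatment is optional, so 240 entrants could also arise from 280 non-remitters at 240/280 = 86% uptake. All of this stands as a limit on the size of the problem. It does not reconcile the two rates, and the text offers neither an uptake figure nor a conservative label.

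Three stronger readings are tempting, and the documents do not support them.

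- *All the effects in Table 1 are too optimistic.* This fails for the four mean rows, which keep more than 80% power at 30%.
- *The true number of remitters will fall below both figures.* A reader might infer this because the Background says "only about 30% to 40% of patients show full remission of their symptoms as defined by the MacArthur criteria", illustrated by a score below 8 with no two-visit condition, while the trial requires that score at two visits. In the same patients the two-visit rule can only lower the rate relative to week 12 alone, or leave it equal. But the article never says the 40% came from that range, it gives the cut-off only as an example, and it contains nothing from which to compute the drop.
- *The trial is too small.* Nothing here shows that.

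**Conclusion.** The inconsistency is real and follows from the printed figures alone: 240 non-remitters and 40 remitters per arm each need a different remission rate for the same endpoint. The largest discrepancies are 53 against 40 remitters per arm (one third more) and 280 against 240 non-remitters.

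The effect on power is modest and uneven. At 30%, only the two proportion rows fall below the stated 0.80, to about 71% and 76%. That rests on two-sided α = 0.01, a pooled-variance test, and the direction of difference that reproduces the table. The mean rows stay at about 84% to 91%, but only because they were evidently computed near 90% power. That is a second mismatch with the stated 0.80, and it should be corrected in the same pass.

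**What to change.** Choose one planning rate, stated for remission at both week 10 and week 12, and use it in both paragraphs. Either adopt 30% throughout, or keep 40% and label 30% explicitly as a conservative scenario with its counts shown alongside.

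From that choice, recompute:

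- every row of Table 1 at the stated α and power, stating sidedness and, for binary predictors, the direction;
- the combination n, which is at most 280 at 30% because entry is optional, with any assumed uptake stated;
- the remitters per arm.

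It may be noted, without a number, that the two-visit rule cannot give a higher rate than week 12 alone.

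The cost is a recalculation and a few reworded sentences. At 30% the proportion rows become about 1 percentage point less favourable, while the mean rows at a true 80% power become slightly more favourable (0.373 against the printed 0.39 to 0.43). Enrolment, conduct and the moderate-to-large conclusion are unchanged.

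### Table 1 does not follow its one stated basis: the continuous rows do not reproduce at 0.80 power, and the serotonin-transporter effect sizes cannot match their own differences

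*Protocol article*

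**What the plan says.** The section Statistical power/sample size sets common assumptions before Table 1. On remission: "For these calculations, we assume a 40% remission rate". On error rates: "a Type I error rate (α) = 0.01, and a statistical power of 0.80". The columns are headed n = 400 (monotherapy) and n = 240 (combination). No separate power, sample size or method is given for continuous and binary variables.

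The contrast is worded in two ways. The aim is that "we will illustrate the effect sizes for treatment remission versus non-remission", but the detectable difference is then defined as "the difference (either mean or proportion) between the population and the treatment remitters detectable with the given sample size". The effect-size column heading describes the difference scaled by the variation.

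After the table the article concludes: "Thus a sample size of 400 will be adequate to detect moderate to large effect sizes in treatment remission predictors".

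**The concern.** With one alpha, one power, one remission rate and two sample sizes, every continuous row should show the same standardised effect within a column, and the binary rows should be close to it. Instead, the n = 400 column runs from 0.31 (transporter) through 0.36 (CRP) to 0.39–0.43 (continuous rows). The n = 240 column runs from 0.40 through 0.48 to 0.50–0.51.

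Table 1 is the only quantitative support for the adequacy statement. A reader who takes it at face value would think that the genetic marker is detectable at a clearly smaller standardised effect than an imaging, endocrine or immune measure. On the stated basis the two are about equal. In a study meant to weigh different kinds of predictor against each other, that is a misleading ranking.

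**Working it through.** **Inputs** (all from Statistical power/sample size and Table 1): remission 40%, so 160 vs 240 of 400 and 96 vs 144 of 240; alpha 0.01; power 0.80; the SDs and population rates in the table. Two choices are mine: the contrast is remitters vs non-remitters, and alpha is two-sided because sidedness is not stated.

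**Continuous rows.** The detectable standardised difference is d = (z₀.₉₉₅ + z_power) × √(1/n₁ + 1/n₂).

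- n = 400: √(1/160 + 1/240) = 0.1021. At 0.80, (2.576 + 0.842) × 0.1021 = 0.349; the non-central t gives 0.350. At 0.90, (2.576 + 1.282) × 0.1021 = 0.394; t gives 0.395.
- n = 240: √(1/96 + 1/144) = 0.1318. At 0.80, 0.450 (t 0.454). At 0.90, 0.508 (t 0.512).

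Multiplying by each SD (non-central t):

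| Row (SD) | Printed | At 0.80 | At 0.90 | Power at the printed value |
|---|---|---|---|---|
| HDRS (4.9) | 1.9 / 2.5 | 1.7 / 2.2 | 1.9 / 2.5 | 0.886 / 0.898 |
| fMRI (4.3) | 1.7 / 2.2 | 1.5 / 1.95 | 1.7 / 2.2 | 0.900 / 0.900 |
| Dex/CRH (266) | 104.6 / 136.1 | 93 / 121 | 105.2 / 136.1 | 0.896 / 0.900 |
| IL-6 (1.4) | 0.6 / 0.7 | 0.49 / 0.63 | 0.55 / 0.72 | 0.946 / 0.883 |

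(HDRS is shown without its minus sign.) None of the eight cells matches at 0.80. Dex/CRH is the sharpest test because it is printed to four figures: 104.6/266 = 0.393 and 136.1/266 = 0.512. The IL-6 effect sizes of 0.43 and 0.50 are the rounded differences divided by 1.4 (0.6/1.4 and 0.7/1.4).

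**Other readings of the continuous rows at 0.80 power:**

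- population vs remitters as two samples (400 vs 160; 240 vs 96): 0.32 / 0.41, further from print;
- remitters against a fixed population value: 0.27 / 0.35, further still;
- 30% remission, the rate used in the paragraph after the table: 0.37 / 0.48, no match;
- 25% remission (100/300; 60/180): 0.396 / 0.513, a close match, but not stated;
- 40% remission with fewer patients: the printed Dex/CRH values need about 318 and 189, i.e. 318/400 = 0.80 and 189/240 = 0.79, also not stated.

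**Binary rows.** Put the population rate p₂ in the non-remitters and p₁ = p₂ − δ in the remitters. Then δ solves δ = 2.576 √[p̄(1 − p̄)(1/n₁ + 1/n₂)] + 0.842 √[p₁(1 − p₁)/n₁ + p₂(1 − p₂)/n₂], with p̄ the weighted mean rate.

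| Row | Printed | Decrease, 0.80 | Decrease, 0.90 | Increase, 0.80 |
|---|---|---|---|---|
| Transporter (59.9%) | 17% / 22% | 17.4% / 22.4% | 19.6% / 25.1% | 16.3% / 20.7% |
| CRP (21%) | 13% / 16% | 12.5% / 15.5% | 13.8% / 16.9% | 15.6% / 20.5% |

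Before rounding to one decimal, the CRP decreases are 12.52% and 15.51%, so they round to the printed 13% and 16%. All four printed cells fit a decrease at 0.80. As increases, the printed CRP differences would have power of only 0.62 and 0.56.

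**Binary effect sizes.**

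- Transporter: SD = √(0.599 × 0.401) = 0.490, so 0.17/0.490 = 0.347 and 0.22/0.490 = 0.449. Cohen's h on the unrounded decreases is 0.349 and 0.451. Printed: 0.31 and 0.40. A binary SD cannot exceed 0.5, so differences of 17% and 22% imply at least 0.34 and 0.44. Allowing for rounding (16.5% and 21.5%) the floor is 0.33 and 0.43, and the smallest possible h is the same to two decimals.
- CRP: SD = √(0.21 × 0.79) = 0.407, so difference/SD is 0.1252/0.407 = 0.31 and 0.1551/0.407 = 0.38. Cohen's h is 0.361 and 0.479, which are the printed 0.36 and 0.48. Using the average of the two groups' variances gives 0.36 and 0.47, so only h fits both cells.

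**The case against.** **The contrast and sidedness are assumed.** That is correct, and the literal definition in the article is population vs remitters. But the article also describes remission versus non-remission, and the literal definition moves the continuous rows further from print. A one-sided alpha would also raise the power at the printed values. Neither choice creates the discrepancy.

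**The heading of the difference columns carries an asterisk, and no note appears in the text available.** The note may only repeat the definition, or it may give a test, direction or sample size. This limits what can be said about the cause. It cannot rescue the transporter effect sizes, which fail against their own differences whatever the power or n.

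**A reader might infer that the continuous rows were computed at 90% power and the binary rows at 0.80.** The article does not establish this. About 25% remission, or about 20% fewer patients, fits the continuous rows about as well. The binary match depends on a direction that is not printed, and only the HDRS row carries a minus sign.

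**The table did not set the sample size.** This stands. The endnote says that 400 replaced 600 because of recruitment, and the section presents the table as an illustration. The consequence is therefore limited to how the table is read.

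**Conclusion.** Table 1 is internally inconsistent. At the stated 40% remission, alpha 0.01 and power 0.80, the continuous rows should show 0.35 and 0.45 SD. The Dex/CRH row overstates this by 12 to 13% (0.393/0.350 and 0.512/0.454). This rests on remitters vs non-remitters and a two-sided alpha; none of the other contrasts tried restores agreement. The cause cannot be identified from the article.

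The transporter effect sizes are wrong regardless of those assumptions. They are about 11% too small (0.31/0.349 and 0.40/0.451). The CRP effect sizes are on a different measure from the one in the column heading.

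A reader might go on to infer that 400 patients are too few. The documents do not support that. The continuous-row error is conservative: at 0.80 power the design detects smaller effects than those printed, so the adequacy statement for moderate to large effects stands. Only the transporter effect size errs in the flattering direction, and its corrected value is still no larger than that of the continuous rows.

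**What to change.** Recompute every row on one basis and print it with the table: contrast, group sizes, sidedness, power, direction for the binary rows, and one named effect-size measure calculated from unrounded differences. With remitters vs non-remitters at 160/240 and 96/144, two-sided alpha 0.01 and power 0.80, the entries would be:

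- HDRS −1.7 / −2.2; fMRI 1.5 / 1.95; Dex/CRH about 93 / 121; IL-6 0.49 / 0.63; each with effect size 0.35 / 0.45;
- transporter 17% / 22% as decreases, effect size about 0.35 / 0.45;
- CRP 13% / 16% as decreases, effect size either labelled as Cohen's h (0.36 / 0.48) or given as difference/SD (about 0.31 / 0.38).

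If a smaller n, an attrition allowance or another remission rate was intended, apply it to all rows and state it. If the population-vs-remitters contrast was intended, recompute all rows on that and drop the other wording.

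The cost is a corrected table and a sentence or two of text. Nothing in the conduct of the trial changes.
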